### Data management

For systematic data management, electronic data capture of Medicallogic Company (www.medicallogic.com) will be used for this study. During the study, the electronic case report form for each enrolled participant will be filled in with all data, which includes the baseline visit, and clinical data, such as comorbidities. All relevant data will be uploaded from the source documents into an electronic case report form by study-site personnel. This web-based platform will be accessible for permitted research team members only.

### Statistical analysis

All data will be analyzed using IBM SPSS Statistics version 28.0.1 (Armonk, New York, USA) and a significance level of 5% will be set with a 95% confidence interval. Patient demographics will be calculated using descriptive statistics. Kolmogorov–Smirnov test will be performed to assess the distribution of data. To compare baselines between the two groups, a student’s t-test and chi-squared test will be conducted. In case the randomization is not balanced, the baseline difference will be corrected through multivariate logistic regression and analyzed. To compare the mean difference, if the primary outcome (skeletal muscle mass) data in both groups are found to be normally distributed, we will perform an independent t-test. Missing data will be handled depending on the distribution of data after study completion. To investigate the effects of the interventions and differences between groups for secondary outcomes, a mixed effects model or generalized estimating equations will be conducted, with one between-subject factor (group) and one within-subject factor (evaluation time).

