### Primary outcome

The primary objective of this study is to determine the effect of mobile application and wearable smart band in the management of prognostic factors in colorectal cancer patients. Therefore, the primary outcome would be the skeletal muscle mass increment in the intervention group compared to the control group in 12 months from the baseline, measured using the bio impedance analysis.

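### The only covariate correction named is a logistic regression applied on observed baseline imbalance; it does not fit a continuous primary outcome compared as a mean difference

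*Protocol article*

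**What the plan says.** All the relevant text is in the Methods of the protocol article.

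- Primary outcome: "the primary outcome would be the skeletal muscle mass increment in the intervention group compared to the control group in 12 months from the baseline". It is obtained by bioimpedance and is a continuous quantity.
- Statistical analysis, primary comparison: "if the primary outcome (skeletal muscle mass) data in both groups are found to be normally distributed, we will perform an independent t-test". The stated aim of that sentence is a difference in means.
- Statistical analysis, baseline: "To compare baselines between the two groups, a student’s t-test and chi-squared test will be conducted". The next sentence is the correction rule: "In case the randomization is not balanced, the baseline difference will be corrected through multivariate logistic regression and analyzed".
- Statistical analysis, secondary outcomes: a mixed model or generalized estimating equations, "with one between-subject factor (group) and one within-subject factor (evaluation time"). No baseline covariate is listed.

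No linear regression, ANCOVA or other covariate adjustment appears. No binary endpoint is defined either. Complications are listed in the visit schedule (Table 2) but not among the outcomes, and the LARS and nutritional scores are each described in three categories.

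**The concern.** Logistic regression models a binary response. An analyst who follows the sentence for the primary outcome must either split muscle mass change at a cut-off that the plan does not give, or model arm membership and add a further step that the plan does not describe. Neither route, as written, leads directly to an adjusted version of the mean difference on which the trial was sized.

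The second problem is the trigger. Correction applies only if randomisation turns out unbalanced, and the rule directly follows the baseline significance tests. No threshold, list of variables or set of covariates is given. Whether an adjusted result exists, and what it adjusts for, is therefore decided after the data have been seen, in a trial whose Randomization section calls it open. This is a method stated wrongly, not a detail left to a fuller document.

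**Working it through.** **Inputs from the article.** Standardised effect 0.35, power 80%, allocation 1 (control) to 2 (intervention), at least 195 and 97 evaluable, 10% drop-out, 324 in total (Sample size calculation); 5% level (Statistical analysis). Sidedness is not stated; two-sided reproduces the stated numbers, while one-sided would need only 76 controls.

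**Inputs assumed.** The correlation r between baseline muscle mass and its change, the number of baseline variables tested, and a p<0.05 trigger. The article gives none of these.

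**Step 1. Reproduce the sample size.** Controls = (1 + 1/2) × (1.960 + 0.842)² / 0.35² = 1.5 × 7.849 / 0.1225 = 96.1, so 97 controls and 194 intervention patients. For a two-sided t-test at 97/195, the noncentrality is 0.35 × √(97 × 195 / 292) = 0.35 × 8.048 = 2.817 on 290 degrees of freedom, which gives power 0.802. With drop-out, 292 / 0.9 = 324.4, against the stated 324. The design therefore rests on a difference in means.

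**Step 2. Set the model beside the endpoint.** The endpoint is continuous, its test is an independent t-test of means, and its sizing is a standardised mean difference. The correction is a model for a binary response. The sentence names neither the response nor the covariates, so the adjusted estimate is undefined.

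**Step 3. How often could the trigger fire?** Under correct randomisation with k independent tests at 5%, P(at least one p<0.05) = 1 − 0.95^k:

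- k = 1: 5%
- k = 5: 23%
- k = 10: 40%
- k = 20: 64%

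Correlated variables would lower these figures.

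**Step 4. What does the trigger cost if the adjustment itself is valid?** Simulation with 97/195 patients, one baseline covariate, a linear adjustment, and 8,000 runs per setting. The conditional strategy adjusts only when the baseline t-test has p<0.05.

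| Setting | Never adjusted | Always adjusted | Adjusted only on imbalance |
|---|---|---|---|
| Type I error, r = 0.3 | 0.045 | 0.048 | 0.044 |
| Type I error, r = 0.5 | 0.048 | 0.050 | 0.043 |
| Power at 0.35, r = 0.3 | 0.804 | 0.839 | 0.807 |
| Power at 0.35, r = 0.5 | 0.803 | 0.899 | 0.816 |

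The formula agrees for routine adjustment. The residual SD shrinks by √(1 − r²), so normal-approximation power at 97/194 is 0.808 (r = 0.1), 0.839 (r = 0.3) and 0.901 (r = 0.5), against 0.804 unadjusted.

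The simulation isolates the trigger. It uses one baseline test and a linear model, so it does not measure the effect of using a logistic model.

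**The case against.** The strongest defence is that the sentence concerns the baseline difference and names no outcome. The primary outcome has its own test in the next sentence, and nothing says that the t-test is replaced. The words may be a slip for linear regression. All of this stands, and it limits the harm: the main test can be run and is powered as stated. It does not rescue the rule, which as written still cannot be carried out on the only primary endpoint.

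Four stronger readings are tempting, and the document does not support them.

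- *Muscle mass change will be dichotomised and power will fall.* A median split would indeed cut efficiency to about 2/π = 0.637. The effect would act like 0.35 × √0.637 = 0.279, and power would be about 0.61. But no section plans a cut-off, so this figure does not describe the trial's plan.
- *The data will choose between two primary analyses on different scales.* The text does not say that an odds ratio takes over from the mean difference.
- *Logistic regression can never lead to an adjusted mean difference.* A logistic model of arm membership could serve as a propensity score and give one. The article does not describe that step.
- *Baseline tests in a randomised trial only detect chance.* Here the Randomization section places baseline assessment after open allocation, so a difference could also reflect knowledge of the arm.

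It is also fair to say that an unadjusted t-test on change is valid under randomisation, and that the conditional strategy keeps power at or above the design's 80%. The precision loss is a gain forgone, not a failure to meet the design.

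**Conclusion.** The point holds as a should-fix. The plan names one covariate correction, of a type that does not match its continuous primary outcome, and makes its use depend on observed imbalance without saying how imbalance is judged or what is adjusted for.

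Its size is moderate. The sample size and the unadjusted primary test are unaffected, and type I error under conditional adjustment is about 4.3% to 4.4%. What is lost is a usable adjusted estimate if the rule is invoked, freedom from after-the-fact choice, and roughly 3 to 8 points of power (0.839 − 0.807 and 0.899 − 0.816). The power figures rest on assumed correlations of 0.3 to 0.5. The 40% and 64% trigger probabilities rest on an assumed 5% rule with 10 or 20 independent tests.

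**What to change.** Replace the correction sentence with wording such as: *The treatment effect on skeletal muscle mass will be estimated by linear regression (ANCOVA) of the 12-month value on arm and baseline skeletal muscle mass, whatever the observed baseline balance. Baseline characteristics will be summarised descriptively by arm, without significance tests. Logistic regression will be used for binary outcomes only.*

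Using the change instead of the 12-month value as the response gives the same arm effect once baseline is in the model. Centre may be added, since there are three hospitals; the article describes no stratification that would require it. Any further covariates should be listed before outcome data are examined.

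The cost is one short passage of text. Table 2 already schedules body composition at baseline and 12 months, so no data, visits or patients are added. The stated sample size suffices, with power of 0.81 to 0.90 for assumed correlations of 0.1 to 0.5.

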### Sample size calculation

Based on a previous study [24], the sample size was calculated with effect size of 0.35 (moderate level), 80% of power, and allocation ratio 1 (control group): 2 (intervention group) using the G-power 3.1.9.2. The results showed that the number of intervention and control group participants were at least 195 and 97, respectively. Considering the drop-out rate (10%), total number of participants was 324 (216 of intervention group and 108 of control group). We will enroll competitively participants to reach target sample size.

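### The primary t-test is gated on a normality check it does not need and leaves baseline muscle mass out as a covariate; a prespecified baseline-adjusted linear model is a nearly free improvement

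*Protocol article*

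**What the plan says.** The Primary outcome section defines the endpoint, measured by bioimpedance, as "skeletal muscle mass increment in the intervention group compared to the control group in 12 months from the baseline".

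The Statistical analysis section speaks of comparing the mean difference and then gives the rule: "if the primary outcome (skeletal muscle mass) data in both groups are found to be normally distributed, we will perform an independent t-test". The distribution check is named just before: "Kolmogorov–Smirnov test will be performed to assess the distribution of data". No primary test is named for data that fail it. The mixed model or generalized estimating equations in the same section are assigned to the secondary outcomes.

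That section contains one form of baseline correction. If randomization turns out unbalanced, the baseline difference is to be corrected by multivariate logistic regression. Table 2 schedules body composition at baseline and at every follow-up visit, so baseline muscle mass is planned for everyone.

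On size, the Sample size calculation section uses "effect size of 0.35 (moderate level), 80% of power, and allocation ratio 1 (control group): 2 (intervention group") and reports that "the number of intervention and control group participants were at least 195 and 97, respectively". It gives neither an SD nor the scale of the effect size.

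**The concern.** Four features of the primary analysis deserve attention.

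- **The gate.** The only named primary test is conditional on a feature of the outcome data. If the check fails, the article does not say what replaces it. The study is described as open under Randomization, allocation, and blinding, so a replacement chosen after seeing outcome data would be hard to defend.
- **The baseline value.** It is planned for everyone and is likely to be strongly correlated with the 12-month value, but it is not a prespecified covariate. Precision is left unused.
- **The label.** The parenthesis in the t-test sentence says skeletal muscle mass, while the outcome section says increment. The two should name the same quantity.
- **The correction.** Logistic regression models a binary outcome; skeletal muscle mass is continuous. Using an observed imbalance as the trigger also makes the primary analysis depend on the data.

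**Working it through.** **Inputs from the article.** Effect size d = 0.35; power 80%; allocation 1:2; evaluable numbers 97 control and 195 intervention; 5% significance level. Sidedness is not stated.

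**Inputs assumed.** Correlation ρ between baseline and 12-month muscle mass, range 0.5 to 0.9; equal SDs at the two times; the distributions used for the gate.

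**1. The plan's own figure.** Normal approximation, two-sided 5%, two intervention patients per control:

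n(control) = (1 + 1/2) × (1.960 + 0.842)² / 0.35² = 1.5 × 7.849 / 0.1225 = 96.1, so 97 control and 194 intervention.

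With 97/195 the noncentrality is 0.35 × √(97 × 195 / 292) = 0.35 × 8.048 = 2.817, and noncentral-t power on 290 df is 80.2%. The stated numbers reproduce as a two-sided unadjusted t-test. A one-sided test would need only 76 controls and does not reproduce them.

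**2. Change-score t-test against baseline adjustment.** In units of the 12-month variance, the residual variance is 2(1 − ρ) for the change score and 1 − ρ² for the baseline-adjusted model (ANCOVA). Their ratio is (1 − ρ²) / [2(1 − ρ)] = (1 + ρ)/2. If d = 0.35 is in change-score SDs, the ANCOVA noncentrality is 2.817 / √[(1 + ρ)/2]:

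| ρ (assumed) | Variance ratio | Noncentrality | ANCOVA power | Change-score power |
|---|---|---|---|---|
| 0.5 | 0.75 | 3.253 | 90% | 80% |
| 0.7 | 0.85 | 3.055 | 86% | 80% |
| 0.8 | 0.90 | 2.969 | 84% | 80% |
| 0.9 | 0.95 | 2.890 | 82% | 80% |

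**3. Which quantity is tested, and on which scale d is expressed.** If raw 12-month mass were tested and d were in change-score SDs, the effect in 12-month SDs would be 0.35 × √[2(1 − ρ)]. That is 0.350, 0.271, 0.221 and 0.157 at ρ = 0.5, 0.7, 0.8 and 0.9, with power 80, 59, 43 and 24%. If d is instead in 12-month SDs, the test on raw 12-month mass has 80.2% power at any ρ. The change-score test then has 80, 95 and 99% at ρ = 0.5, 0.7 and 0.8, and ANCOVA 90, 98 and more than 99%. Power therefore drops below 80% in this setting only if three conditions hold together: raw mass is tested, d is in change-score SDs, and ρ exceeds 0.5.

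**4. The gate.** Simulated trials of 97/195, with failure counted when either arm rejects normality at 5%. Distributions are assumptions: t with 6 df, and a two-sex mixture (60% men with mean 30 kg, SD 4; women with mean 21 kg, SD 3).

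| Distribution | Lilliefors-corrected | Uncorrected Kolmogorov–Smirnov | t-test type I error |
|---|---|---|---|
| t, 6 df | 53% | 3.5% | about 5% |
| Two-sex mixture | 73% | 2% | about 5% |

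Repeat runs moved these rates by a few points (51–53% and 73–77% corrected; 2–4% uncorrected). With truly normal data the corrected version fails in about 9% of trials, because two tests are run at 5% each. The mixture describes raw mass and bears less on the increment.

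**The case against.** The best defence is that a t-test on increments is valid, is matched to the sample size calculation and meets its 80% target. Preferring ANCOVA is then a matter of efficiency, worth only about 2 points at ρ = 0.9. That stands, and it is why this is an improvement and not a failure of the design.

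A reader might infer that the plan throws away the baseline value. The documents do not support this. The outcome is an increment from baseline and the analysis section speaks of a mean difference, so baseline enters by subtraction.

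A reader might also infer that power falls to 59, 43 or 24%. That needs the three conditions in step 3 together. The sample size section does not state the scale of d, and raw mass is the less natural reading.

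Nor can one say that the gate will usually fail. The article does not specify which version of the Kolmogorov–Smirnov test applies, and the assumed distributions do not come from it.

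Finally, this is a condensed article, and a fallback test may stand in an analysis plan that is not shown. It is fair to say only that the article names none. The gate itself, however, is fixed in the article, and so is the logistic correction.

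**Conclusion.** The point holds as a free improvement, with one element wrong as written.

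- The normality gate is unnecessary at 195/97. Type I error stays near 5% without it under the assumed distributions. Whether the named test is run at all could turn on a software option: 2–4% failure against 53–73%.
- The change-score t-test is valid but less efficient than adjustment for baseline: 80% power against 90, 86, 84 or 82% at assumed ρ of 0.5, 0.7, 0.8 or 0.9, if d is in change-score SDs.
- The label in the t-test sentence should be aligned with the increment in the outcome definition.
- The imbalance-triggered logistic correction does not fit a continuous outcome.

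The stated sample size reproduces, and no failure of the stated 80% power is demonstrated.

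**What to change.** Prespecify one primary analysis: a linear model of 12-month skeletal muscle mass on group and baseline skeletal muscle mass, reporting the adjusted mean difference with its 95% confidence interval. Sex and centre may be added as covariates. With baseline in the model, the group coefficient is the same whether the response is the 12-month value or the increment, so the model also answers the question in the outcome definition.

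Delete the normality condition and the imbalance-triggered logistic step for this outcome. Keep a rank-based test as a sensitivity analysis only. Use the same name for the outcome in the Primary outcome, Sample size calculation and Statistical analysis sections, and state the scale of the 0.35.

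The cost is wording. The model runs in the planned software, needs no new data, and leaves the sample size at 324 enrolled.

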### Outcome measures

Outcomes will be assessed at baseline and at 1-, 3-, 6-, and 12-month follow-ups. Outcome measures will be assessed by clinical research coordinator and summary of baseline screening, assessment, and follow-up during study visits is described in Table 2.

**Table 2 Tab2:** Summary of baseline screening, assessment, and follow-up during study visits

		STUDY PERIOD				
		Post-allocation				
TIMEPOINT		*Post op* *(± 1w)*	*1-month* *(± 2w)*	*3-month* *(± 1 m)*	*6-month* *(± 2 m)*	*12-month* *(± 2 m)*

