	**INTERVENTIONS**:					
	***Personalized digital therapeutic (intervention) group***					
	***Control group***					
	**ASSESSMENTS**:					
***7***	***Complication***		X	X	X	X
***8***	***Hb, albumin***	X ^1)^			X	X
***9***	***CT (visceral fat, muscle mass)***	X ^1)^			X	X
***10***	***Body composition***	X	X	X	X	X
***11***	***EORCT-QLQ-C30***	X	X	X	X	X
***12***	***EORCT-QLQ-CR29***	X	X	X	X	X
***13***	***MNA***	X	X	X	X	X
***14***	***IPAQ-SF***		X	X	X	X
***15***	***Grip strength***	X	X	X	X	X
***16***	***30 s chair stands test***		X	X	X	X
***17***	***2 min walk test***		X	X	X	X
***18***	^***a***^ ***LARS***		X	X	X	X
***19***	^***b***^ ***Satisfaction questionnaire***				X	

*CT*: computed tomography, *EORCT-QLQ*: European Organization for Research and Treatment of Cancer-Quality of life Questionnaire, *MNA*: Mini Nutritional Assessment, *IPAQ-SF*: International Physical Activity Questionnaire-Short Form, *LARS*: Low Anterior Resection Syndrome Score Questionnaire

^a^ Rectal cancer without ileostomy and colostomy.

^b^ Digital therapeutic group only.

^1)^ Tests analyzed within previous 6 months from the baseline can be collected.

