### Participant safety and withdrawal

The researcher’s name and phone number for an emergency contact will be provided to ensure the patient’s safety. All participants are informed that they can voluntarily discontinue the study at any time and they could be withdrawn when the significant disease non-related to study is detected, cancer metastasis and recurrence occurs, or if they did not follow the instruction of doctor in charge.

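### The missing-data method for the primary outcome is left to be chosen after completion from the data, although repeated muscle readings that could inform it are collected

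*Protocol article*

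**What the plan says.** All references are to the protocol article.

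- **Missing data (Statistical analysis).** The whole rule is "Missing data will be handled depending on the distribution of data after study completion". It follows directly after the primary-outcome test. No method is named, and no separate rule is given for the primary outcome.
- **Primary outcome.** It is "skeletal muscle mass increment in the intervention group compared to the control group in 12 months from the baseline", by bioimpedance. The test is conditional: "if the primary outcome (skeletal muscle mass) data in both groups are found to be normally distributed, we will perform an independent t-test".
- **Repeated-measures model.** It is assigned elsewhere: to examine "differences between groups for secondary outcomes, a mixed effects model or generalized estimating equations will be conducted".
- **Schedule.** "Outcomes will be assessed at baseline and at 1-, 3-, 6-, and 12-month follow-ups". In Table 2 the row "Body composition" is marked at all five visits.
- **Openness.** Randomization, allocation, and blinding describes an open study in which participants and evaluators can tell the assigned arm. The abstract calls the trial single-blinded, but this section is the specific one, and I rely on it.
- **Sources of loss.** The sample size allows for 10% dropout. Participant safety and withdrawal permits withdrawal when "cancer metastasis and recurrence occurs, or if they did not follow the instruction of doctor in charge".

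**The concern.** Three features act together.

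**Timing.** The method is to be settled after completion, when anyone analysing this open trial can see what each option does to the result. The primary p-value can then be selected, even without intent.

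**Criterion.** The choice between completers, imputation and likelihood methods turns on why values are missing. The distribution of the values that were observed does not answer that.

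**Unused information.** A two-sample t-test on 12-month change takes nothing from the 1-, 3- and 6-month readings. Those readings are the best available evidence on patients who leave before month 12. The plan already contains a model that would use them, but not for the endpoint that matters most.

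Loss related to outcome is plausible here. Recurrence and failure to follow instructions are grounds for withdrawal, and only the intervention arm has an app to keep up with. If such loss differs between arms, a completers comparison is biased.

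**Working it through.** **1. The plan's own figure.** Inputs from Sample size calculation: effect size 0.35, power 80%, allocation 1:2. Alpha is 5% (Statistical analysis). Two-sided is my assumption, since sidedness is not stated.

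n(control) = (1 + 1/2) × (1.960 + 0.842)² / 0.35² = 1.5 × 7.85 / 0.1225 ≈ 96.1. With the t-distribution this becomes 97, so 194 intervention. Power is 80.1% at 97/194 and 80.2% at the stated 97/195. A one-sided test would give 76/152, which does not match. Then 292 / 0.9 = 324.4 against the stated 324. The sample size is sound, and it already covers the power lost to 10% dropout. The issue is bias and choice of method.

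**2. Bias of a completers t-test.** The document gives no SD, correlation or dropout pattern, so these are assumptions:

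- 216/108 patients, and changes in SD units;
- correlation ρ = 0.7 between 6- and 12-month change (range 0.5 to 0.85);
- log-odds of loss before month 12 = a − b·z, where z is the 6-month change and a is set to give the stated loss;
- no true effect.

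With R(z) the probability of being retained, the bias from one affected arm is ρ × E[z·R(z)] / E[R(z)].

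| Affected arm(s) | Slope b | Loss | Mean z if retained | Bias, ρ = 0.7 | ρ = 0.5 to 0.85 |
|---|---|---|---|---|---|
| Both alike | 1 | 10% | 0.091 in each | 0.064 − 0.064 = 0 | 0 |
| Intervention only | 0.3 | 10% | 0.030 | 0.021 | 0.015 to 0.025 |
| Intervention only | 1 | 10% | 0.091 | 0.064 | 0.045 to 0.077 |
| Intervention only | 1 | 20% | 0.173 | 0.121 | 0.087 to 0.147 |

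Relative to the design effect of 0.35, the last three rows are 0.021/0.35 = 6%, 0.064/0.35 = 18% and 0.121/0.35 = 35%.

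**3. False positives.** At 10% loss the standard error is √(1/194 + 1/97) = 0.124.

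- Strong slope: shift 0.064/0.124 ≈ 0.51. P(Z > 1.45) + P(Z < −2.47) ≈ 0.074 + 0.007 = 8%.
- Weak slope: shift 0.021/0.124 ≈ 0.17, giving about 5%.
- Strong slope, 20% loss (173/86): standard error 0.132, shift 0.92, giving about 15%. Simulation gives 16 to 17%.

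Simulation agrees with the rest: about +0.06 SD and 8% in the strong case, and about 0 and 5% when both arms behave alike. If the affected arm is the control arm, the sign reverses: a true effect of 0.35 is estimated at 0.35 − 0.064 ≈ 0.29, with power about 65%.

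**4. A likelihood estimate using the 6-month value.** In the same settings its bias is close to zero, because loss depends only on a value that the model uses.

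**5. Choosing afterwards.** A separate illustrative simulation took the most favourable of four analyses: completers, last observation carried forward, baseline carried forward, and likelihood. The false-positive rate was about 7 to 8% even with dropout alike in both arms, and about 13 to 31% with one-arm outcome-related dropout at roughly 10 to 20% nominal loss. The document names none of the four as its method, so these figures are a ceiling on what a free choice permits. They do not forecast what this team would do.

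**The case against.** **About 32 patients are discarded.** A reader might infer that the t-test drops everyone without a 12-month value, about 10% of 324. The document does not say so. It names no method, and a t-test after multiple imputation would fit its wording and could draw on the earlier visits. What stands is narrower: the named test does not by itself use those readings, and nothing commits the analyst to a method that would.

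**The word distribution may mean the pattern of missingness.** That reading is possible in a condensed article. The nearby Kolmogorov–Smirnov sentence makes observed values the more natural one. On either reading the choice still waits until completion.

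**The bias depends on the assumptions.** This is fair. It needs outcome-related loss that differs between arms. It vanishes when the arms behave alike and is small with a weak slope.

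**The mixed model is not a cure.** Also fair. Its lack of bias holds under missing at random. If half the dropouts had no 6-month reading, an estimate using only that visit kept a bias of +0.029 SD. If loss depended on the 12-month value itself, the bias was +0.049 against +0.091 for completers. Withdrawal for recurrence could act that way, hence the sensitivity analysis.

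**A t-test on change is legitimate, and GEE is not an error.** Both are correct. A pre-specified t-test with a pre-specified missing-data method would be defensible. Choosing between a mixed model and GEE for secondary outcomes is commonly settled in a statistical analysis plan, and GEE suits categorical outcomes such as LARS class. I make no criticism there.

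**It belongs in the analysis plan.** Silence would. This sentence instead fixes a time and a criterion, and an analysis plan naming a method in advance would contradict it.

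**Conclusion.** The point holds in this form: the protocol ties the missing-data method to data seen after completion of an open trial, on a criterion that does not bear on why values are missing, and it keeps its repeated-measures model away from the primary outcome. Confidence is high on the deferral and moderate on the consequences.

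The size is conditional. With 10% loss, correlation 0.7 and no true effect, the bias of a completers analysis runs from none (arms alike), through about 0.02 SD (weak, one arm), to about 0.06 SD with about 8% false positives (strong, one arm). At 20% loss the strong case reaches about 0.12 SD and 16 to 17%. None of the correlation, slope or dropout pattern comes from the document. The document does not support a claim that the primary result will be biased, or that a complete-case analysis is planned. The change should be made, but it does not call the design or the sample size into question.

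**What to change.** Delete the sentence. By dated amendment or analysis plan, before outcomes are compared by arm, specify:

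1. **One primary analysis.** A mixed model for repeated measures of skeletal muscle mass at 1, 3, 6 and 12 months, with baseline skeletal muscle mass as covariate and group by visit. The 12-month group contrast is the primary estimate. State that it is valid under missing at random. Further covariates and the covariance structure can be left to the analysis plan.
2. **One sensitivity analysis under missing not at random.** A delta adjustment of the unobserved 12-month values, with the range of deltas fixed in advance.

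The cost is wording and a little more analysis work. The sample size, the visits and the measurements stay as they are. Patients with no reading after baseline still contribute nothing to the primary model, so loss should be reported by arm and by visit.
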